## Methods: monitoring

### Data monitoring

The trial will be conducted according to the Good Clinical Practice (GCP) guidelines and will be monitored by the GCP unit at the University of Copenhagen.

### Harms

The included patients will be instructed to contact the principal investigator or a trained sub-investigator (doctor) in case they experience any events with possible relation to the trial treatment within the study period. Additionally, at the follow-up visits, all new medical events and any new medications that the patients have received throughout the trial will be thoroughly examined by the principal investigator or a trained sub-investigator. Any adverse events during or after the treatment in the trial will be noted and categorised into severity according to the Common Terminology Criteria for Adverse Events version 5.0 (CTCAE vs 5.0). The onset date, duration, and action taken for the adverse event will be documented.

Adverse events are defined as any untoward medical occurrence in the clinical trial period. All adverse events of CTCAE grade 3 and 4, and incidences considered related to this trial will be reported to the sponsor by the investigator immediately after they are discovered.

A serious adverse event is defined as a medical event that results in the following:DeathA serious deterioration in health including:Resulted in life-threatening illness or injuryRequired hospitalisation or prolongation of existing hospitalisationResulted in permanent impairment of body structure or body functionResulted in medical or surgical treatment to prevent the aboveAnything the principal investigator deems to be of clinically serious significance

Any serious adverse events will be reported to the Danish Medical Agency and the National Health Committee along with a report on the patients’ safety once a year. In case of a serious adverse event deemed related to the treatment, the Danish Medical Agency and the National Health Committee will be noted within 15 days or 7 days in case of death or life-threatening events.

Adverse events will be monitored for the first 4 months after the treatment. Serious adverse events will be monitored for the 12-month study period.

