### Outcomes

The primary endpoint is to evaluate the impact of ASC injections on unstimulated salivary gland function compared to placebo in patients with previous head and neck cancer. The change is evaluated from baseline to month four.

Secondary endpoints are as follows:

To compare the effect of ASC injection, relative to placebo, from baseline to month four on all of the following outcome measurements:Change in stimulated salivary gland function.Change in the patient-reported outcome of xerostomia: The European Organisation for Research and Treatment of Cancer Quality of Life Questionnaire, Head and Neck-35 (EORTC QLQ-H&N35):Domains for dry mouth (HNDR)Domains for sticky saliva (HNSS)Domains for swallowing (HNSW)Change in the patient-reported outcome of xerostomia: Xerostomia Questionnaire (XQ).Change in the composition of salivaSafety evaluated by the development of treatment-related adverse events, serious adverse reactions, or deathImmune response to allogeneic ASC measured by the development of de novo HLA

Tertiary outcomes are as follows:

The change in unstimulated whole salivary flow rate, stimulated whole salivary flow rate, patient-reported outcome of xerostomia evaluated by two questionnaires (EORTC QLQ-H&N35 and XQ), composition of saliva, safety, and immune response in patients receiving ASC injection compared to placebo is further evaluated at 12 months.

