Patients are followed up after 4 month (+/− 14 days) and after 12 months (+/− 4 weeks). At the follow-up visits, patients will undergo saliva flow measurements, have analyses of saliva composition, have blood samples taken (for HLA antibodies), fill out QoL questionnaires, and have an ultrasound exam of the submandibular salivary glands. Lastly, all adverse events are monitored throughout the study period, from the time of treatment until the last day of follow-up (Fig. 1). When all study participants have completed the 4-month follow-up data will be unblinded. All data will be documented on-site in a secure web database, REDCap (Fig. 2).

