## Methods: data collection, management, and analysis

### Data collection methods

Data is collected at baseline and at follow-up visits at 4 months (+/− 14 days) and after 12 months (+/− 4 weeks) by the principal investigator or a sub-investigator (doctor). Data are recorded on case report forms (CRFs). Unstimulated whole salivary flow rate and stimulated whole salivary flow rate will be collected by sialometry, and recorded in the CRF immediately after collection. The saliva will be saved and stored in a −80 °C freezer until use. All saliva samples stored in the freezer will be recorded and documented in a freezer log. Patient-reported outcomes will be assessed using the two questionnaires, the EORTC QLQ-H&N35, with a focus on domains for dry mouth (HNDR), domains for sticky saliva (HNSS), and domains for swallowing (HNSW), and the XQ. The patients can answer the questionnaires on-site or at home via unique links sent directly to the database. All adverse events are monitored during the trial. Blood samples will be collected at all the visits to monitor the development of HLA antibodies. The results obtained from the blood samples are directly entered into the patient’s medical record by the laboratory.

Any data insertions or corrections in the CRF will automatically be noted in a data log audit trail. The log audit identifies and records all activities carried out by each individual user, including the data accessed or modified, as well as the patients’ record IDs. A data management plan for the will be completed.

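### The protocol gives two collection windows for adverse events, so it is undefined whether the 12-month safety comparison covers non-serious events after month 4; separately, apart from death, the safety endpoint counts only events judged related to treatment

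*Protocol article*

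**What the plan says.** The protocol article describes the adverse-event window in several places.

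- Participant timeline: "all adverse events are monitored throughout the study period, from the time of treatment until the last day of follow-up". Follow-up visits are at 4 and 12 months.
- Data collection methods: "All adverse events are monitored during the trial".
- Harms, definition: "Adverse events are defined as any untoward medical occurrence in the clinical trial period".
- Harms, follow-up visits: "all new medical events and any new medications that the patients have received throughout the trial will be thoroughly examined".
- Harms, closing lines: "Adverse events will be monitored for the first 4 months after the treatment", followed by "Serious adverse events will be monitored for the 12-month study period".

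The Outcomes section makes safety a secondary endpoint at month 4. It has three parts: adverse events related to treatment, serious adverse reactions, and death. Among the tertiary outcomes, "composition of saliva, safety, and immune response in patients receiving ASC injection compared to placebo is further evaluated at 12 months".

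The Participant timeline and Statistical methods sections unblind the data once every patient has completed the 4-month visit. The Eligibility criteria make pregnancy, site infection, smoking, and recurrence or new cancer reasons for withdrawal.

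**The concern.** The collection window decides which events enter the database. A statistical analysis plan written later can choose how to tabulate events, but it cannot recover events that sites were told not to collect. If the closing lines of Harms govern, the non-serious part of the 12-month safety outcome has no monitoring rule behind it after month 4. If the Participant timeline governs, it is complete. Staff who follow different sections could also record different things.

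The second issue is what the endpoint counts. With a randomised placebo arm, harm can be estimated by comparing all events between arms, without asking anyone to attribute cause. An endpoint that requires a relatedness judgement gives up part of that protection. The article's own risk section acknowledges unsettled evidence on whether these cells affect tumour growth. An investigator could readily attribute a recurrence to the original cancer and not to the injection.

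**Working it through.** The plan states no figure on this point, so the check is a comparison of the text, with simple date arithmetic at the end.

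**Step 1. The windows side by side**

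| Section | Events | Window |
|---|---|---|
| Participant timeline | all adverse events | treatment to last follow-up day (month 12) |
| Data collection methods | all adverse events | the whole trial |
| Harms, definition | all adverse events | the whole trial |
| Harms, follow-up visits | all new medical events | the whole trial |
| Harms, closing lines | adverse events | first 4 months |
| Harms, closing lines | serious adverse events | 12 months |

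The 4-month sentence disagrees with two other sections and with two statements in its own section. The term study period adds to the ambiguity: the pregnancy exclusion uses it for 4 months, and Harms uses it for 12.

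**Step 2. What each reading leaves of the 12-month safety outcome**

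| Component | Participant timeline governs | Harms closing lines govern |
|---|---|---|
| Related non-serious events, to month 4 | covered | covered |
| Related non-serious events, months 4 to 12 | covered | outside the monitoring rule |
| Serious adverse reactions, to month 12 | covered | covered |
| Deaths, to month 12 | covered | covered (death is a criterion for a serious event) |

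One row of four depends on the reading. The disputed span is 12 − 4 = 8 months.

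**Step 3. Recording versus counting**

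Take a non-fatal recurrence in month 8, judged unrelated.

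- It would most likely be recorded. It is a withdrawal reason. It would also plausibly be a serious event, since the definition covers treatment given to prevent death or lasting impairment and anything the principal investigator considers clinically serious.
- It would not count towards the endpoint. It is not a related adverse event, not a serious adverse reaction, and not a death.

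The restriction therefore lies in the endpoint, not in data collection.

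**Step 4. How far the month-4 unblinding could reach**

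Inputs from Trial status: recruitment from February 2021 to February 2023 (24 months), and last visit expected in February 2024.

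- Last treatment: February 2024 − 12 months = about February 2023.
- Last 4-month visit, and so the earliest unblinding: February 2023 + 4 months = about June 2023.
- Patients still in follow-up then: those treated after June 2023 − 12 months = June 2022.
- That is about 8 of the 24 recruitment months. At an even pace, and with treatment soon after enrolment, 8/24 = one third of patients would have some part of months 4 to 12 after unblinding.

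This ignores the visit windows and the interval of up to 90 days between baseline and injection. It bounds who could be affected. It does not show that anyone judging causality knew the allocation.

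**The case against.** Several stronger readings are tempting, and the document does not support them.

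- A reader might infer that the 12-month safety comparison cannot be made. It can be made in full under the Participant timeline. Under the Harms closing lines it can still be made for serious reactions and deaths. The outcome is also ranked as tertiary.
- A reader might infer that eight of the twelve months go unobserved for non-serious events. Harms itself has new medical events over the whole trial examined at the follow-up visits, and month 12 is one of those visits. The text supports an ambiguous window, not a known gap.
- A reader might infer that late cancers would be missed by design. Step 3 shows that a recurrence would probably be documented on two routes.
- A reader might say that the endpoint counts related events only. Death carries no such condition.

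It is also fair to say that a related-event endpoint is a design choice, that Harms records and grades events whatever their cause, and that all-cause tables are commonly left to an analysis plan, which is not shown here. On unblinding, patients treated early had finished before it could happen. The Allocation section restricts the randomisation table to one person until the end of the trial, and nothing says that the doctors judging causality learn individual allocations.

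These points limit the finding but leave two things standing. The window sentences contradict one another on what is collected, and no analysis plan can settle that afterwards. The named endpoint does leave out a recorded, non-fatal event judged unrelated, whatever additional tables may be planned.

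**Conclusion.** The contradiction is real and is on the face of the document. It leaves one component of the 12-month safety outcome undefined: non-serious adverse events in months 4 to 12. Serious adverse reactions and deaths are unaffected.

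The dependence on judged causality is a separate and lesser weakness. It does not prevent a 12-month comparison, but it makes every component except death rest on an investigator's opinion. For some patients that opinion may be formed after unblinding. The last point assumes that unblinding the data makes allocation known to those judging causality, which the article does not state. The one-third figure further assumes even recruitment and prompt treatment.

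No effect on event counts can be calculated from the document, because it gives no expected adverse-event rates. The issue should be corrected because the fix is cheap. It does not threaten the primary endpoint.

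**What to change.** 1. Reconcile the Participant timeline, Data collection methods and Harms sections to one adverse-event collection window that covers the 12-month safety outcome, and use study period in one sense throughout.
2. Define the safety comparison as all adverse events and all serious adverse events by randomised arm, regardless of judged causality. Include recurrence or new cancer and site infection, which are already withdrawal criteria. Keep treatment-related events as a secondary display.
3. State whether those who judge relatedness remain unaware of individual allocation after the month-4 analysis.
4. The article was published in September 2023, so some 12-month visits will already have taken place. The report should state which window was applied to those patients.

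The cost is wording, plus slightly more event recording at the 12-month visit, where new medical events are already reviewed. The all-cause comparison uses data that the Harms section already has recorded.

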### Ethical consideration and risk assessment

Participants will receive either ASCs or a placebo into the submandibular salivary glands by a needle, ultrasound-guided. The risk of infection and bleeding is estimated to be below 0.5%. In our previous studies, none of the 40 participants developed adverse reactions [14, 15]. During the injection of the transplant product (ASCs or placebo), the MESRIX-III participants may experience brief pain. There is a controversial debate regarding the effect of ASCs on cancer growth, as they have been shown to have both inhibitory and stimulatory effects [21–25]. However, multiple clinical trials have been conducted on different participant populations, including local injection of stem cells, involving more than 1000 participants, and no increase in the incidence of cancer has been detected. Extensive research has been carried out on the use of ex vivo expanded stem cells, and no data has been found indicating the malignant transformation of expanded human ASCs [26–28]. A study conducted by Katz et al. on a murine model showed that the injection of a high dose of MSC (240 × 106 MSC/kg) did not reveal any signs of cancer, organ toxicity, or change in body weight after 12 months [29].

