### Participant timeline

Patients who are interested in participating in the project will initially be contacted by phone by the investigators for inquiries about their interest in participating in the research project, and to clarify any initial questions. If patients are interested in participating in the project, they are invited to a screening visit at the Department of Otorhinolaryngology, Head and Neck Surgery, and Audiology, Rigshospitalet. Before the visit patients will receive written information regarding the study, the pamphlet “Forsøgspersoners rettigheder i et sundhedsvidenskabeligt forskningsprojekt” (“Rights of test subjects in a health scientific research project”) [19], and the pamphlet “Før du beslutter dig” (“Before deciding”) [20]. Patients are further informed that they have the right to bring a counsel to the screening visit.

The screening visit is conducted by the principal investigator or a trained sub-investigator (doctor). At the screening visit, patients will initially fill out a consent form. When the consent form is completed, inclusion- and exclusion criteria are reviewed with the patients. Patients will have their medical history evaluated, and undergo an ear, nose, and throat examination including an ultrasound exam of the submandibular salivary glands and the neck. If patients meet inclusion criteria so far, they will have whole saliva flow measured by sialometry (Supplementary 2), have blood samples collected and analysed for relevant kidney, infection, and liver parameters, s-HCG when relevant, and for the presence of HLA antibodies. Furthermore, patients will fill out QoL questionnaires (Supplementary 3). Saliva samples collected during the sialometry will be saved for chemical analyses and analyses of saliva composition (Supplementary 4). If patients are eligible for inclusion, they are randomised in a 1:1 ratio to receive ultrasound-guided injections of either ASCs or placebo in the submandibular glands no later than 90 days after the baseline visit. If patients fulfil one or more exclusion criteria they will not be included in the study hereafter and will not be randomised. Their data including the salivary samples will not be saved.

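### The safety endpoint counts only related events or deaths, so a non-fatal cancer judged unrelated drops out of the by-arm comparison

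*Protocol article*

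**What the plan says.** The protocol article touches on cancer as a possible harm in four places.

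- **Ethical consideration and risk assessment** raises the mechanism: "There is a controversial debate regarding the effect of ASCs on cancer growth, as they have been shown to have both inhibitory and stimulatory effects". It goes on to cite trials of stem cells in various populations, "involving more than 1000 participants, and no increase in the incidence of cancer has been detected", and reports no evidence of malignant transformation of expanded cells.
- **Eligibility criteria** requires two recurrence-free years after the head and neck cancer and makes recurrence or a new primary (basocellular carcinoma excepted) a reason for withdrawal.
- **Outcomes** defines safety at month 4 by three items: adverse events related to treatment, serious adverse reactions, and death. The tertiary outcomes extend this without a new definition: "safety, and immune response in patients receiving ASC injection compared to placebo is further evaluated at 12 months".
- **Harms** records events more widely. "Adverse events are defined as any untoward medical occurrence in the clinical trial period", with no condition on cause. At follow-up visits, "all new medical events and any new medications that the patients have received throughout the trial will be thoroughly examined". Serious adverse events are followed for 12 months, and all of them go to the authorities.

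No listed outcome names recurrence or new primary cancer.

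**The concern.** Data collection is broad but the endpoint is narrow. Two of its three items require a judgement that the treatment caused the event; the third is death. For most harms such a filter is tolerable. It suits this one badly, because every participant has a prior cancer that offers a ready alternative explanation for a recurrence. If the cells raised the recurrence rate, an extra case would look the same as a background case, and an investigator who does not know the allocation has no basis for telling them apart. An excess would appear only as a difference in counts between arms, taken without regard to attribution.

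At stake is the wording of the safety conclusion. Followed as written, the trial could report no treatment-related events and no deaths while saying nothing by arm about the cancers that occurred, although it has a randomised placebo group and the records needed. The primary efficacy result is not affected.

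**Working it through.** The article gives no cancer rate, so there is no figure of its own to reproduce. The first step is textual; the others show how much a count could tell.

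**Step 1. Follow one event through the text.** Take a non-fatal neck recurrence at month 8, judged unrelated.

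- Withdrawal criterion (Eligibility criteria): met, so recorded.
- Adverse event (Harms): met, since the definition ignores cause.
- Serious adverse event (Harms): usually met, through hospitalisation, treatment to prevent serious deterioration, or the principal investigator's judgement. It is then reported to the authorities.
- Safety endpoint, related adverse event (Outcomes): not met.
- Safety endpoint, serious adverse reaction (Outcomes): not met on the usual meaning of a reaction, an event with a suspected causal link. Harms defines the serious adverse event separately and treats those deemed related as a subset.
- Safety endpoint, death (Outcomes): not met.
- 12-month safety comparison (Outcomes): not met, as it carries no definition of its own.

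The event is captured in the records and absent from the stated between-arm endpoint.

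**Step 2. Expected number of cancers.** Inputs: 60 per arm (Abstract); 12-month risk of 2%, 3% or 5% (assumption).

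- Expected count = 60 × p: 60 × 0.02 = 1.2; 60 × 0.03 = 1.8; 60 × 0.05 = 3.0.
- If the cells doubled the risk, the active arm would expect 2.4, 3.6 and 6.0.
- Chance of at least one cancer in the placebo arm = 1 − (1 − p)^60: 70%, 84% and 95%.

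Some cancers are therefore likely under these assumptions. In the extreme case where all are non-fatal and judged unrelated, the endpoint shows 0 against 0, whatever the true difference.

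**Step 3. Power of a by-arm count.** Normal approximation, two-sided 5%, n = 60 per arm, with p̄ the mean of the two risks:

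Power = Φ{[|p1 − p0| − 1.96 × √(2p̄(1 − p̄)/n)] / √([p0(1 − p0) + p1(1 − p1)]/n)}

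- 2% against 4%: (0.02 − 1.96 × 0.0311) / 0.0311 = −1.32, so power is 9%.
- 3% against 6%: 12%.
- 5% against 10%: (0.05 − 1.96 × 0.0481) / 0.0479 = −0.92, so power is 18%.
- For a tripling of risk: 20%, 28% and 45%.

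The approximation is rough at such small counts, but the message is clear.

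**Step 4. What zero events would mean.** Exact two-sided 95% upper limit for 0 of n = 1 − 0.025^(1/n).

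- n = 60: 1 − 0.025^(1/60) = 6.0%.
- n = 48, if the planned 20% dropout also removed cancer status (60 × 0.8 = 48): 1 − 0.025^(1/48) = 7.4%.

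**The case against.** The strongest reply is that nothing is hidden. Harms defines adverse events without regard to cause, has new medical events reviewed at visits, follows serious events for 12 months and reports all of them to the authorities. Cancer also triggers withdrawal. A reader might infer from the endpoint that a cancer could go unreported; the article does not support that, and this part of the reply stands in full.

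A second reply is that tables by arm belong in the analysis plan, which is not shown. Such a plan may well tabulate all serious events by arm, and nothing in the article forbids it. This stands only in part. The point is not a missing table: the article states the endpoint, and the endpoint carries a causality condition. An all-cause serious-event table would meet most of the concern if it showed cancers on their own line.

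Third, the risk should not be overstated. The article balances its remark on stimulation with more than 1000 participants and no observed increase. That is fair, and it would be wrong to call cancer an established hazard of the cells. The article describes those trials as covering different populations and does not say that they were previous head and neck cancer patients injected in the neck. The reassurance is relevant but not decisive here.

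Fourth, a reader might infer that neck recurrences will be missed because the screening visit includes "an ultrasound exam of the submandibular salivary glands and the neck" while the follow-up visits list only that patients "fill out QoL questionnaires, and have an ultrasound exam of the submandibular salivary glands". The text does not carry this. The neck scan sits among the eligibility checks, no neck-imaging outcome is defined, and the follow-up sentence may be shorthand.

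Finally, the count would have little power. That is correct, and it limits what the outcome can show. It is also a reason to print the interval, since a bare statement of no related events conveys none of that uncertainty.

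**Conclusion.** The concern holds in a limited form. The stated safety endpoint selects on judged causality, and a non-fatal recurrence or new primary judged unrelated falls outside the comparison with placebo at both 4 and 12 months, although the article itself raises possible effects on cancer growth. The defect lies in what is compared between arms, not in what is recorded or reported to the authorities.

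Its size cannot be fixed from the document. With an assumed 12-month risk of 2 to 5%, between 1.2 and 3 cancers per arm are expected without any effect, and up to all of them could be excluded. How often a recurrence would be judged unrelated is also an assumption. The corrected count would be descriptive: power for a doubling is 9 to 18%, and zero events among 60 would not exclude a risk of 6.0%. The conclusion also rests on reading a serious adverse reaction in its usual causal sense. If the sponsor meant any serious adverse event, the wording should say so, and most of the gap would close.

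**What to change.** Add one descriptive safety outcome: recurrent or new primary cancer, basocellular carcinoma excepted, from injection to month 12, counted whatever the judged relation to treatment. Report it by randomised arm as counts, an exact 95% interval for each arm, and the risk difference. Count patients withdrawn because of cancer as events, and state how many in each arm had unknown cancer status at month 12. Draw the data from the withdrawal, adverse-event and serious-event records. No extra visit or imaging is needed.

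The cost is one outcome line and one table. Statistical methods says the analysis plan will be completed before the end of the study, and Trial status anticipates the last visit in February 2024, so there was room for this when the article appeared in September 2023. Data are unblinded once all month-4 visits are complete, so an outcome added after that point should be dated and labelled as such. The remaining downside is wide intervals and a more cautious safety statement.
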